### Measures

A series of previously validated and reliable self report measures will be administered by mail. Domain specific quality of life (QOL) will be included as a potential moderator of intervention effect and challenge appraisals and therapeutic alliance as mediators. Primary outcomes are: sexual adjustment; unmet sexual supportive care needs; masculine self-esteem; marital satisfaction; utilisation of erectile aids. Secondary outcomes are: psychological distress; overall QOL and benefit finding. Disease variables (e.g. cancer grade, stage) will be assessed through medical and cancer registry records review. Use of medical services and associated costs will be assessed through Medicare Australia records.

#### Moderators/Mediators

##### Domain specific QOL

The International Prostate Symptom Score [32] and the urinary and bowel symptom subscales of the UCLA Prostate Cancer Index [33] will assess disease specific QOL. Women will complete a menopausal symptom scale derived from the Breast Cancer Prevention Trial (BCPT) Symptom Checklist [34].

##### Challenge appraisal

A person's cognitive appraisal of an event will determine if that event is perceived as stressful and this will be assessed using a Stress Appraisal Measure based on the work of Roesch [35].

##### Therapeutic alliance

The quality of the bond between the peer and nurse counsellors and the couple and extent of agreement about therapy goals will be assessed by the Working Alliance Inventory [36].

#### Primary Outcome Variables

##### Sexual function

Men will complete the International Index of Erectile Functioning (IIEF) [37], which allows sexual function to be assessed in five domains: erectile function, orgasmic function, sexual desire, intercourse satisfaction and overall sexual satisfaction. Women will complete the Female Sexual Function Index (FSFI) [38]. This questionnaire parallels the IIEF and examines sexual function among women in six domains: sexual desire, arousal, lubrication, orgasm, satisfaction, and pain.

##### Sexual Supportive Care Needs

Couples needs related to sexual relationships will be assessed using the sexuality needs subscale of the Supportive Care Needs Survey [39,40].

##### Sexual Self-Confidence

The Short Form Psychological and Interpersonal Relationship Scale (SF-PAIRS) [41] will assess sexual confidence and spontaneity associated with ED.

##### Masculine Self-Esteem

The Masculine Self-Esteem scale will assess men's appraisal of their masculinity [42].

##### Utilisation of sexual aids

A scale developed by Schover [43] will assess whether men have obtained medical help for sexual dysfunction and the impact of each treatment on their sex life.

##### Marital satisfaction

An abbreviated version of the Dyadic Adjustment Scale (A-DAS) [44] will assess marital satisfaction among couples.

#### Secondary Outcome Variables

##### Psychological Distress

The Hospital Anxiety and Depression Scale [45] will provide a global measure of current psychological distress with subscale scores for anxiety and depression.

##### Quality of Life

Health related quality of life will be assessed with the SF-36, the most widely used QOL measure in the world with norms for the Australian general population available. The SF-36 [46] contains a mental health and physical health summary scale to measure the impact of the intervention on patients' and partners' wellbeing.

##### Benefit Finding

Benefit finding [47] will be used to measure the perceived positive experiences and outcomes (eg appreciation of life, changes in life priorities) resulting from the diagnosis of cancer.

### Statistical Analyses

The study hypotheses will be tested by multilevel modelling (MLM). This class of procedures is the appropriate way to analyse hierarchical data sets such as the longitudinal data of the proposed research in which observations are nested within persons who in turn are nested within couples. Study condition is modelled as a fixed effect at the couple level. The typical RCT effects that have been tested by ANOVAs are all available with MLM; however there are several fundamental differences between the statistical models. First, in MLM individual and couple trajectories of change in time can be modelled directly as random effects. This provides appropriate tests of Hypotheses 1 and 2 and allows precise examination of predictors of individual versus group change. Second, MLM minimises the loss of data through attrition in that unlike ANOVA all available data points from participants are included in analyses. The direct ML estimation normally used in MLM is currently the most favoured technique (along with multiple imputation) for minimising bias and enhancing precision in parameter estimates from incomplete data [48]. Hypotheses 1 and 2 will be tested with appropriate contrasts on the fixed effect of study condition. Although power calculations from multilevel longitudinal analyses are not as well articulated as for older techniques, the study will have at least as much power as the equivalent ANOVA (i.e., 80% for a moderate effect size;) as the intervention effects are all based upon the level 3 (i.e., couple) sample size.

A cost-utility analysis will also be undertaken to address Hypothesis 3 where intervention resources and health outcomes are combined in an analysis to produce information on the relative economic efficiency between the peer, nurse specialist and usual care options. The analysis will take the perspectives of the health provider and health system and involve the assessment of 1) cost data on resources used in each of the three arms by identifying, quantifying and valuing resources using standard methods and, 2) health outcomes, in terms of quality-adjusted life years (QALYs). Using Medicare Australia data, we also wish to capture health utilisation costs for GP visits and medication use to assess whether the interventions change typical health care use. Quality of life will be measured in participants using the preference-based utility instrument SF-6D [49] which is based on the SF-36 quality of life tool. The key outcome for the cost-utility analysis will be the *incremental cost-effectiveness ratio*, expressed as the incremental cost per QALY. This ratio represents the difference in costs between the intervention and usual care options divided by the difference in QALYs gained across the two options. This means that it is the *additional *cost and health benefits of each of the two interventions over and above what occurs in usual care that is important. Secondary economic endpoints will include incremental cost-effectiveness ratios for cost per % gain in sexual function and psychological distress. A Bayesian statistical approach to the analysis will be followed so that probabilistic statements on the efficiency of the intervention will be produced [50]. Data will be analysed using the computer program TreeAge Pro (Healthcare Module) 2005 [51]. The results will be scrutinised using probabilistic sensitivity analysis which is standard practice in economic evaluations to address data uncertainty and potentially strengthens the generalisability of the results. Specifically, Monte Carlo simulations will produce cost-effectiveness acceptability curves and probabilistic statements on cost-effectiveness.

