### Approaches to Intervention Delivery

By contrast to women, men are less likely to seek help for psychological distress; are under-represented as clients to cancer support services; are reluctant to utilise effective sexual aids after prostate cancer treatment *despite *high levels of dissatisfaction with the sexual outcomes of treatment. Effective support interventions need to utilise delivery methods and sources that are acceptable to this patient group. Men and their partners prefer individual consultations for sexuality support after prostate cancer [16]. Tele-delivered interventions are highly acceptable to this group, and web/computer based programs are frequently accessed by men for medical and procedural information [24,25]. Remote access delivery methods overcome geographical barriers to access and so are applicable to geographically dispersed populations with high potential for population-based translation.

A source of support that has high uptake amongst men with prostate cancer in Australia and internationally is peer support, with men reporting that peer discussions provide informational and emotional support and reduce feelings of social isolation [26]. A feasibility study of a dyadic peer support program for men with prostate cancer reported reduced depression and improved self efficacy in the short term, with men most frequently discussing incontinence, erectile dysfunction and Prostate-Specific Antigen testing with their matched peers [27]. As well, a randomised controlled trial of a group education program to assist men to adjust to prostate cancer treatments [28] found that only by adding peer discussion to the provision of information by an expert was sexual bother alleviated significantly, relative to a control group. An advantage of peer support that is provided by veteran patients is that it is inexpensive by comparison to professionally delivered approaches, such as specialist nurses. While this approach is highly promising, to date randomised controlled trials to assess the effectiveness of peer support in improving men's adjustment have not been undertaken. However, based on research to date a peer delivered counselling intervention paired with education may have equal efficacy to health professional delivery. As well, the relative cost savings for a peer support approach as compared to professional approaches, although not yet quantified, make this a potentially cost effective source of support.

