## Methods/Design

### Study Aims and Hypotheses

The overall study aim is to compare the efficacy of peer-delivered telephone support with DVD educational resource, vs. oncology nurse-delivered telephone counselling with DVD educational resource, vs. usual care in improving both men's and women's sexual and psychosocial adjustment at 3, 6 and 12 months after treatment for localised prostate cancer. In doing so we will also compare the cost-effectiveness of support by trained peers vs. nurse counsellors; and identify demographic, medical and psychosocial variables that predict improvement in psychosexual adjustment in prostate cancer patients and their partners with each intervention approach.

The intervention will utilise a cognitive behavioural approach that has been found to be effective in promoting positive adjustment after cancer [30], along with couple relationship education focussed on relationship enhancement and helping the couple to conjointly manage the stresses of cancer diagnosis and treatment [19]. The study will have three arms: (1) usual care (2) telephone support by a trained male peer support volunteer who is a prostate cancer survivor with DVD education and (3) oncology nurse-delivered telephone counselling with DVD education.

It is hypothesised that 3, 6, and 12 months after surgery for localised prostate cancer:

1. By contrast to couples in usual care, couples who receive either the peer or nurse delivered intervention will have a more positive sexual adjustment; lower unmet sexuality supportive care needs; more positive attitudes to sexual help seeking; higher uptake of erectile aids; improved psychological adjustment and quality of life.

2. Couples who receive the peer and nurse delivered intervention will have similar sexual adjustment; sexuality supportive care needs; attitudes to sexual help seeking; uptake of erectile aids; psychological adjustment and quality of life.

3. The peer delivered intervention will be more cost effective by comparison to the nurse delivered intervention.

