### Participants

With the strong endorsement and support of Queensland Urologists, patients will be referred to the project from private urology practices and public hospital outpatient clinics in Queensland, Australia. Informed written consent will be obtained by study trained research nurses who will contact potential participants after referral to the study. We will recruit 70 couples per condition over a 12 month period (allowing for 10% attrition from treatment; 210 couples in total to be recruited). Assuming a moderate effect size of d = 0.5, alpha at .05, the resulting power with 70 couples per condition is 0.8. Inclusion criteria are that the men must: (1) have been newly diagnosed with localised prostate cancer and have chosen radical prostatectomy as their treatment approach (2) be currently in a heterosexual cohabitating couple relationship (3) be able to read and speak English (4) have no previous history of head injury, dementia or psychiatric illness (5) have no other concurrent cancer. As the intervention has been developed based on previous data for heterosexual couples this intervention is unlikely to be helpful for homosexual couples.

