## Discussion

This study will address a critical but as yet unanswered research question: to identify a cost-effective and population based approach to promoting optimal psychosexual adjustment for men with prostate cancer and their partners. To date, for this patient group, no sexuality intervention studies have: targeted couples at diagnosis when distress is highest; been adequately powered to look differentially at intervention effects; trialled peer support; or included economic analyses. This research will overcome these limitations. The intervention will be able to be utilised by trained nurses in a range of settings including broad reach tele-health lines and also through peer support programs that are conducted internationally. This means that project outputs will be immediately translatable into practice to improve the sexual health and overall well-being of men with prostate cancer and their partners.

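### Hypothesis 2 claims that peer and nurse delivery are similar, but the stated contrast and the stated power are those of a test for a difference and cannot support that claim

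*Protocol article*

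**What the plan says.** Under Study Aims and Hypotheses, Hypothesis 1 is a superiority claim for either active arm over usual care. Hypothesis 2 is of another kind: "Couples who receive the peer and nurse delivered intervention will have similar sexual adjustment", and the same is predicted for the other listed outcomes. The Background (Approaches to Intervention Delivery) gives the reason, that "a peer delivered counselling intervention paired with education may have equal efficacy to health professional delivery".

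The Statistical Analyses section states one method for both: "Hypotheses 1 and 2 will be tested with appropriate contrasts on the fixed effect of study condition". It describes the multilevel model as giving appropriate tests of the two hypotheses.

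The Participants section gives the sample size: "Assuming a moderate effect size of d = 0.5, alpha at .05, the resulting power with 70 couples per condition is 0.8", with 10% attrition allowed for. The Statistical Analyses section repeats 80% power for a moderate effect, by analogy with ANOVA. The article states no margin, no confidence-interval rule and no power for concluding similarity.

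**The concern.** A contrast on the condition effect, used as a test, can reject equality of the two active arms but cannot establish it. If Hypothesis 2 has the same kind of test as Hypothesis 1, the only result that can favour it is failure to reject. Noisier data then make that result more likely. The quoted 0.8 is no protection, because it is the chance of finding a difference of 0.5 SD and not the chance of showing that a difference is small.

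Whether trained peers can do what nurse counsellors do is one of the trial's main questions. Two active arms that were equally ineffective would also look similar, so a similarity finding needs to be read together with Hypothesis 1.

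**Working it through.** **Inputs from the article.** d = 0.5, alpha 0.05, power 0.8, 70 couples per arm, 10% attrition (Participants); equal allocation (Study Integrity); follow-up at 3, 6 and 12 months (Study Aims and Hypotheses). **Assumed, because the article gives no values:** the margins, the correlations between visits, and two-sided alpha. All results are in units of the single-visit SD and use the normal approximation.

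**1. The stated power.** 70 × 0.9 = 63 evaluable couples per arm. SE of a pairwise difference = √(2/63) = 0.178. Power = Φ(0.5/0.178 − 1.96) = 0.80. The quoted figure is therefore right for a two-sided pairwise test of a difference.

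**2. How often the peer–nurse contrast is non-significant when the arms truly differ by δ** (one time point, unadjusted): Φ(1.96 − δ/0.178) − Φ(−1.96 − δ/0.178).

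| True δ (SD) | 0.20 | 0.25 | 0.30 | 0.40 | 0.50 |
|---|---|---|---|---|---|
| P(non-significant) | 80% | 71% | 61% | 39% | 20% |

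The 95% half-width is 1.96 × 0.178 = 0.35. A result that just misses significance, at 0.35 SD, has an interval reaching about 0.70 SD, beyond the 0.5 SD used for sizing.

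**3. Power to conclude equivalence if the arms are truly equal.** TOST at 5% on each side, margin m: max(0, 2Φ(m/SE − 1.645) − 1).

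Three analyses are compared, all with 63 couples per arm:

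- One time point, unadjusted: SE = 0.178.
- One time point, adjusted for baseline with correlation r = 0.5: SE = 0.178 × √(1 − 0.25) = 0.154.
- Mean of three follow-ups, adjusted for baseline, with all correlations equal to r: SE = 0.178 × √[(1 + 2r)/3 − r²]. At r = 0.5 the bracket is 0.417 and SE = 0.115. At r = 0.7 the bracket is 0.310 and SE = 0.099.

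| Analysis | 95% half-width | m = 0.25 | m = 0.30 | m = 0.40 | m = 0.50 |
|---|---|---|---|---|---|
| One time point, unadjusted | 0.35 | 0% | 3% | 45% | 75% |
| One time point, r = 0.5 | 0.30 | 0% | 24% | 66% | 89% |
| Follow-up mean, r = 0.5 | 0.23 | 40% | 66% | 93% | 99% |
| Follow-up mean, r = 0.7 | 0.19 | 62% | 83% | 98% | >99% |

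**4. Reading the margins.** A margin of 0.50 SD equals the whole effect the trial is sized to detect. Peer delivery could fall short of nurse delivery by almost that much and still be called similar. A useful margin has to be clearly smaller, and then the choice of contrast decides whether the trial can support it.

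**The case against.** The case on the other side has four parts.

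- **The wording permits a correct analysis.** A contrast yields an estimate and a standard error, and an equivalence test uses the same two quantities. The article does not say that the contrast is against zero, or that a non-significant result will be reported as similarity. A reader might infer both. The inference is natural, since one sentence serves both hypotheses and the only power is for a difference, but the text does not state it.
- **A margin might stand in a fuller document.** This carries weight against a complaint of mere omission. It does not excuse what the article itself fixes: it names one kind of test, calls it appropriate for a similarity hypothesis, and gives a difference-based power as the power for both. A margin also bears on the sample size, which the article does set.
- **The sample may be more informative than one time point suggests.** This stands. A reader might conclude that the trial cannot rule out a worthwhile difference, but the documents do not support so flat a statement. The planned model uses repeated measurements, and under the assumed correlations its power at a 0.30 SD margin could be 66% to 83%. If each time point is judged separately, the less favourable rows apply.
- **Other analyses share the load.** The cost-utility analysis carries uncertainty forward without a significance test, and Hypothesis 1 compares the active arms with usual care. This softens the consequence for decisions but gives Hypothesis 2 no test of its own.

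The Discussion says that no earlier study in this patient group has "been adequately powered to look differentially at intervention effects" and that this one will overcome such limitations. That concerns detecting differences. It should not be read as a claim of power for similarity.

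**Conclusion.** The point holds in this form: the article gives a similarity hypothesis the same contrast as a superiority hypothesis, and its only power figure is for detecting d = 0.5. Neither can support Hypothesis 2. The sample-size arithmetic itself is correct for a difference.

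Non-significance is weak evidence here: 71% likely at a true difference of 0.25 SD and 61% at 0.30 SD, for 63 couples per arm at one unadjusted time point. The margin the trial can support is not fixed by the article. At 0.30 SD, equivalence power runs from 3% to about 83% across the analyses considered. That range rests on assumed margins and on assumed equal correlations of 0.5 to 0.7 for the follow-up average. The finding is therefore about the decision rule and the power wording, and it does not show that the sample is inadequate under every reasonable analysis.

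**What to change.** 1. In Statistical Analyses, separate the two hypotheses. For Hypothesis 2, name one primary outcome and one time point (or the average of the follow-ups), and prespecify a margin clearly smaller than 0.5 SD. Conclude similarity only if the 90% confidence interval of the baseline-adjusted peer–nurse contrast lies wholly within that margin.
2. Interpret similarity as similar effectiveness only if at least one active arm beats usual care under Hypothesis 1.
3. If no defensible margin is within reach, recast Hypothesis 2 as estimation of the peer–nurse difference with a confidence interval, and draw no conclusion of similarity.
4. In Participants and in Statistical Analyses, state that the 0.8 power is for detecting a difference of d = 0.5 and does not apply to concluding similarity.

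The cost is wording in the hypothesis, analysis and power text. No extra couples are needed. The drawback is that the trial's stated ability to conclude similarity becomes less favourable.

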### Intervention

Usual care will consist of the man's standard medical management and existing written educational materials. For the two intervention arms, the eight sessions of phone support/counselling will include enhanced couple communication and conjoint coping content and material relevant to the early treatment phase. An audiovisual DVD resource with Tip Sheets will accompany the intervention to enhance the psycho-education and sexuality education components and to also provide actor role models for effective couple communication about sexuality and intimacy. The nurse counselling sessions will follow principles of cognitive-behavioural sex and marital therapy and will utilise an adult learning approach in which partners' self-select goals to focus on while working through the program. Content includes education about prostate cancer, menopause, and sexuality; assigned behavioural homework including increasing expression of affection and non-demanding sexual touch; challenging negative beliefs about prostate cancer, aging, and sexuality; and helping the couple choose a medical treatment for ED that is acceptable to both partners, and integrating this into their sexual relationship. Additional components that target the challenges of the early treatment phase (e.g., urinary incontinence, pain, sleep disturbance, psychological distress) will be additionally selected by the couple if relevant.

Peer support is based on the support partner or 'veteran' patient having personal experience and knowledge about the cancer experience; a unique personal insight into effective ways to cope; and the ability to form a support relationship that is derived from the connection of shared experience. In this way peer support can reduce feelings of isolation and stigma (the sense of being the 'only one'); can convey emotional, social, informational and practical support; and through role modelling can communicate realistic hope and optimism about the future. Peer support volunteers will be prostate cancer survivors who are at least 12 months post treatment and who have support group experience. The intervention will follow the same couples-based approach as the nurse counselling intervention but will be oriented to empathic mutual support and education rather than in depth sex and marital therapy.

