### Study Integrity

Ethical approval has been obtained from the Griffith University Human Research Ethics Committee. The study design will be guided by the CONSORT statement [31]. Randomisation to study condition will occur following the completion of baseline assessment. Assessments will be by self-report pen and paper measures and project staff tracking assessments will be blinded to condition. Randomisation will occur in blocks of 12, with each condition randomly generated 4 times within each block to ensure an unpredictable allocation sequence with equal numbers of couples in each group at the completion of each block. This sequence will be undertaken by the project manager and concealed from investigators. Therapy will be manualised and all intervention calls audiotaped with 25% reviewed to ensure treatment adherence. All analyses will be conducted on the basis of intention to treat.

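### The model and the 80% power stop at the couple and so assume no variance between the nurses or peers delivering the two active arms

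*Protocol article*

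**What the plan says.** The Statistical Analyses section describes a three-level model: repeated observations, within persons, within couples. Study condition is a fixed effect at the couple level, and Hypotheses 1 and 2 are tested by contrasts on it. On power, the section states that "the study will have at least as much power as the equivalent ANOVA", which it puts at 80% for a moderate effect, and gives as its reason "as the intervention effects are all based upon the level 3 (i.e., couple) sample size".

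The 80% comes from the Participants section: "Assuming a moderate effect size of d = 0.5, alpha at .05", and "the resulting power with 70 couples per condition is 0.8". The recruitment target is described as "allowing for 10% attrition from treatment; 210 couples in total to be recruited".

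The Intervention section has oncology nurses or peer volunteers deliver eight telephone sessions in the active arms. Of the volunteers it says: "Peer support volunteers will be prostate cancer survivors who are at least 12 months post treatment and who have support group experience". Usual care has no such provider. Couples, not providers, are randomised: "Randomisation will occur in blocks of 12, with each condition randomly generated 4 times within each block". The alliance measure covers "The quality of the bond between the peer and nurse counsellors and the couple", and the Measures section lists alliance as a mediator. Nowhere does the article mention a provider level, the number of nurses or peers, their caseload, or a provider ICC.

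**The concern.** Randomising couples individually makes them independent at entry. It does not keep them independent once several are treated by the same person. If some nurses or peers do better than others, outcomes within a caseload are correlated, and an arm mean carries provider variance that does not shrink as couples are added to the same caseloads. A model that ends at the couple cannot see that variance.

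Two things are at stake. The contrasts with usual care have one clustered arm. The peer-versus-nurse contrast, which bears on Hypothesis 2 and on the service-delivery question, has two. There, a few unusually strong or weak providers could be read as a property of the delivery model, and the interval used to judge similarity would be too narrow. Second, the stated power rests on the number of couples alone. This is a position that the article takes, not a detail it leaves out: a provider term added in a later analysis plan would still leave the published reason for the 80% wrong.

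**Working it through.** **Inputs from the Participants section.** d = 0.5 (SD = 1), alpha 0.05 (taken as two-sided), 70 couples per arm, 10% attrition, so n = 70 × 0.9 = 63 per arm.

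**Reproducing the plan's figure.** With independent couples the standard error is sqrt(2/63) = 0.178, and 0.5/0.178 = 2.806. Power = Φ(2.806 − 1.96) = Φ(0.846) = 0.801 (0.795 by noncentral t). The stated 0.8 therefore reproduces with two-sided testing and 63 analysed, and it leaves no reserve. With all 70 analysed, the same formula gives 0.841.

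**Assumed inputs, not in the documents.** The number of providers per active arm, k, and the provider ICC. Caseloads are taken as equal, m = 63/k, with the same k in both active arms and each couple belonging to one provider.

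**Formulas.**
- Design effect in an active arm: DE = 1 + (m − 1) × ICC.
- True variance over the variance assumed under independence, R: (DE + 1)/2 for active versus usual care; DE for peer versus nurse.
- Providers ignored: true alpha = 2 × [1 − Φ(1.96/√R)].
- Providers modelled: power = Φ(2.806/√R − 1.96).

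**Worked case, k = 3, ICC = 0.05.** m = 21 and DE = 1 + 20 × 0.05 = 2.0.
- Against usual care: R = 1.5, √R = 1.225. Alpha = 2 × [1 − Φ(1.600)] = 0.11. Power = Φ(2.291 − 1.96) = 0.63.
- Peer versus nurse: R = 2.0, √R = 1.414. Alpha = 2 × [1 − Φ(1.386)] = 0.17. Power = Φ(1.984 − 1.96) = 0.51.

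**Results at 63 per arm** (active versus usual care / peer versus nurse):

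| Providers per arm | ICC | DE | Alpha if providers are ignored | Power if providers are modelled |
|---|---|---|---|---|
| any | 0 | 1.00 | 0.05 / 0.05 | 0.80 / 0.80 |
| 3 | 0.05 | 2.00 | 0.11 / 0.17 | 0.63 / 0.51 |
| 6 | 0.05 | 1.475 | 0.08 / 0.11 | 0.71 / 0.64 |
| 10 | 0.02 | 1.106 | 0.056 / 0.062 | 0.78 / 0.76 |
| 20 | 0.02 | 1.043 | 0.052 / 0.055 | 0.79 / 0.785 |

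The last two columns belong to different analyses and do not occur together. The alpha column is for the planned model. The power column is for a corrected model, whose alpha returns to about 0.05.

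**Small-sample degrees of freedom.** The table uses the normal approximation, which flatters designs with few providers. The Satterthwaite df are (DE + 1)²/[DE²/(k − 1) + 1/(n − 1)] against usual care and 2(k − 1) for peer versus nurse. For k = 3 and ICC 0.05 this gives 9/(4/2 + 1/62) = 4.5 and 4 df, and power of 0.44 / 0.33. For k = 6 and ICC 0.05, power is 0.65 / 0.55.

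**If all 70 couples per arm contribute** (normal approximation). With 5 providers and ICC 0.01, power is 0.82 / 0.795. With 5 providers and ICC 0.05, it is 0.73 / 0.63.

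**The case against.** The strongest reply is that the size of the problem rests on two numbers that the documents do not give. A reader might infer that the standard errors are certainly too small in both arms and that the power claim is simply false. The documents do not support that. Both conclusions need a positive provider ICC and caseloads above one. Peer volunteers may be numerous with one or two couples each, in which case the peer arm is barely affected. The Study Integrity section also has therapy follow a manual, with all calls taped and a quarter reviewed, which may lower the ICC. This stands as a limit on magnitude, but standardising delivery does not make couples who share a provider independent.

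A reader might also infer that one provider takes all eight calls for a couple. The wording for the peer arm suggests it; for the nurse arm it is not stated. If nurses share couples, the simple nesting used in the working would not hold there.

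A third tempting inference is that naming alliance as a mediator shows that the plan expects providers to differ. It does not: alliance can vary from couple to couple under one provider and still mediate.

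The comparison with ANOVA is relative, and the ANOVA has no provider level either, so clustering undermines the 80% and not that comparison. The planned model also uses all available data; with all 70 couples per arm, independent power is 0.84 and small clustering is largely absorbed.

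Finally, provider numbers, caseloads and the degrees-of-freedom method are commonly left to a fuller document, and their absence is no fault here. What remains is the stated top level and the stated basis for power.

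**Conclusion.** The point holds in conditional form. The article fixes the couple as the top level and rests its power on the number of couples, which amounts to assuming zero variance between providers. At 63 evaluable couples per arm the 80% has no margin, so in this calculation any positive ICC with more than one couple per provider takes power below the 80.1% obtained under independence. Over the assumed cases shown, and by normal approximation, the harm runs from slight (20 providers, ICC 0.02) to serious (3 providers, ICC 0.05: alpha of 0.11 and 0.17 if providers are ignored, or power of 0.63 and 0.51 if they are modelled), and it is always larger for peer versus nurse. The proper description of the 80% is unsupported, not disproved. The missing level is certain from the text; its numerical effect is not. These figures also assume equal caseloads, one provider per couple and the same number of providers in both active arms.

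**What to change.** - Record a provider identifier for every couple and every call, so that shared couples can be recognised. Providers already log partner participation and minutes for each session, so this is one more field, and it is far easier to secure prospectively.
- Fit a partially nested model: a provider random effect in the peer and nurse arms only, none in usual care, with Satterthwaite or Kenward-Roger degrees of freedom.
- Replace the sentence that claims at least the ANOVA's power of 80% with power for each contrast over the planned number of providers and an assumed range of ICCs, stating whether 63 or 70 couples per arm are taken to contribute.

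The cost is one variable and one random term, somewhat wider intervals and a somewhat lower stated power.
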